### Data Collection

#### Overview

Data sources for assessing feasibility and acceptability outcomes described further in the following sections include (1) web analytics (eg, participant log-ins, page views, and visit times), which capture data needed to assess program adherence; (2) module completion surveys, which are embedded in the web-based program and assess program acceptability; (3) program completion surveys, administered through REDCap, which assess program acceptability and barriers to completion among all participants enrolled in the study; (4) baseline and 90-day follow-up surveys, also administered through REDCap, which access constructs in the program conceptual model (Figure 2); and (5) the web-based screener and study participant contact tracking database, which will be populated by program staff and will capture data on recruitment, eligibility, enrollment, and retention.

#### Website Use Data

Website use data will include the number of program log-ins, pages viewed, visit times, and modules completed. In addition, the participants will be offered the opportunity to rate the selected videos and activities from 1 to 5 stars. Altogether, ratings and website use data will inform our understanding of the acceptability of videos and activities and allow for the assessment of program engagement and adherence.

#### Module Completion Surveys

Brief (1- to 2-minute) module completion surveys will be embedded in the web-based program. These surveys will appear at the end of each module and solicit mother and teenager feedback on module acceptability and any technical problems encountered. Mothers and teenagers will be asked to complete separate surveys before proceeding to the next module.

#### Program Completion Surveys

Both mothers and teenagers will be asked to complete the program completion surveys, which will be administered through REDCap. The links to the surveys will be emailed to the mothers after completion of the final module. Surveys will assess program acceptability indicators (Textbox 2), as well as barriers to completion and suggestions for program improvement. Mothers and teenagers who do not complete the program within the 8-week implementation period, including those who never log into the program or those who log in but do not complete any modules, will be sent a program completion survey tailored to their completion level.

#### Baseline and Follow-up Surveys

Baseline and follow-up surveys, administered to mothers and teenagers through REDCap at enrollment and 90 days following enrollment, will assess the demographic characteristics of participants, including both the mother’s and teenager’s past exposure to IPV (baseline only), as well as cognitions, skills, and behaviors targeted by the eMTSD program. The collection of these data will allow us to describe study participants; gauge survey length and completion rates; assess psychometric properties of key measures; and explore pre-post changes in the cognition, skills, and behaviors targeted by the program (Figure 2, program conceptual model).

#### Web-Based Screener and Recruitment Tracking Data

The web-based screener will capture data on recruitment sources and participant demographics (eg, race, ethnicity, and sex). A study tracking database will capture data on staff contacts with potential participants, telephone eligibility screens, participant enrollment, program log-in, survey completion reminders, and incentive disbursements. These data will be used to explore the effectiveness of different recruitment strategies for identifying individuals who meet the study inclusion criteria by recruitment source and participant characteristics.

### Statistical Analysis

#### Overview

Descriptive statistics will be used to summarize the demographic characteristics of the study population and feasibility and acceptability indicators for the sample. Bivariate statistical procedures (eg, 2-tailed *t* tests and chi-square tests) will be used to examine associations between demographic and background characteristics of mother and teenager participants (age of the mother; sex, gender identity, and race and ethnicity of the teenager; family financial stress; mother and teenager psychological distress; and mother and teenager IPV exposure) and (1) recruitment source (eg, Facebook advertisement, domestic violence agency), (2) program adherence, (3) program acceptability, and (4) study retention. These analyses will help identify potential sources of bias and characterize program feasibility and acceptability as a function of participants’ demographic characteristics.

Descriptive statistics will be used to summarize adherence rates by *adherence support* group, and bivariate statistics will be used to examine differences between groups in adherence indicators (program log-in and initiation rates and program adherence). Paired *t* tests and McNemar test will be used to examine trends in pre-post changes in cognition, skills, and behaviors targeted for change by the program (Figure 2) among program completers. These analyses are considered exploratory, given that the study is not powered to assess changes in these constructs.

#### Power

We used the approach described by Lewis et al [29] to determine the sample size for this feasibility and acceptability trial. This approach uses a *traffic light* system to evaluate the progression to the main trial based on a set of a priori criteria. Hypothesis testing for binary feasibility outcomes tests against being in the red zone (unacceptable outcome) based on the expectation of being in the green zone (acceptable outcome). Using this approach, an adequate sample size is that which gives high power (≥80%) to reject being in the *red zone* if the *green zone* holds true.

Three focal feasibility and acceptability outcomes were selected to determine the sample size: (1) enrollment rate, (2) overall program acceptability, (3) teenager program initiations, and (4) program completion rates. The point estimates that will be considered the red zone upper limit (R_ul_) and green zone lower limit (G_ll_) for these outcomes are (1) the proportion of those eligible from those who enroll (R_ul_=0.60 and G_ll_=0.75), (2) the proportion of those who agree or strongly agree that the program is acceptable across all indicators >0.60 (R_ul_=0.55 and G_ll_=0.75), (3) the proportion of those enrolled who initiated the use of the program with their teenager >0.50 (R_ul_=0.50 and G_ll_=0.65), and (4) the proportion of those enrolled who completed the program >0.30 (R_ul_=0.30 and G_ll_=0.50). The null hypothesis test, for which the sample size is calculated, is that the true outcome is not greater than R_ul._

Table 3 shows that a sample size of 100 provides >80% power to reject the null hypothesis across each of the focal feasibility and acceptability outcomes, with an α of .05 and a 1-tailed, 1-sample binomial test based on normal approximation (with continuity correction).

**Table 3 table3:** Power for focal binary feasibility and acceptability outcomes.

Outcome	Red zone upper limit, %	Green zone lower limit, %	Power^a^, %	N^b^
Enrollment rate (percentage of those eligible who enroll)	60	75	80	68
Program acceptability (percentage of those completing the program who agree or strongly that the program is acceptable across all domains)	55	75	80	40
Teenager program initiation rate (percentage of those enrolled who start the program with their teenager)	50	65	80	73
Program completion rate (within group; percentage of those assigned to the group who complete all 6 program modules)	25	50	80	25 (per group; 100 overall)

^a^Power (1-B) to reject being in the *red zone* if the *green zone* holds true.

^b^Needed sample size for the hypothesis test.

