Given that the MTSD program was found to have positive impacts, the next step in the continuum of research on the program is to optimize the program for dissemination (ie, distribution of the program by the community and other agencies to mothers exposed to IPV and their teenagers) and implementation (ie, use of the program by mothers and their teenagers within the real-world family setting). Notably, the MTSD program was structured to avoid 2 main obstacles in the implementation of family-based interventions. First, it avoids logistical barriers that prevent families from attending programs offered at out-of-home locations as the program can be conducted at home (or at any location the family chooses). Second, there are no costs associated with training or paying the delivery staff as the program is self-administered. However, the drawbacks of the program from a dissemination and implementation (D&I) standpoint include the costs of printing and mailing (eg, through the postal service) the booklets, which may be prohibitive to organizations serving mothers exposed to IPV, which are typically low-resourced community-based organizations [12]; insufficient reach to low-literacy members of the target population, given the relatively high reading burden of the program; and a lack of built-in prompts or cues to engage with the program, which may result in poor user engagement in real-world settings. For example, in the MTSD randomized controlled trial, which provided small financial incentives for booklet completion, 62% of families reported completing the final booklet [11].

The research team proposed that each of these D&I barriers could be addressed by adapting the program for web-based delivery. In particular, web-based delivery has the potential to reduce dissemination costs; allow for the audiovisual presentation of information and activities, thus potentially reducing the reading burden and improving understanding among audiences with lower health literacy [13,14]; and allow for automated delivery of reminders, tailored based on website use, to maximize program uptake and completion. Furthermore, the research team postulated that a digital platform for MTSD may increase program appeal among teenager participants, given research suggesting that there has been a pronounced shift among US teenagers away from the use of *legacy* media (eg, books) and toward digital media [15].

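### The acceptability progression criterion carries two thresholds, 0.60 and 0.55; Table 3's N of 40 is right for 0.55, and its power depends on completers with survey data, not on the 100 enrolled

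*Protocol article*

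**What the plan says.** The Power section adopts a traffic-light approach with progression criteria set in advance, under which "an adequate sample size is that which gives high power (≥80%) to reject being in the *red zone* if the *green zone* holds true". The hypothesis is defined once for all outcomes: "The null hypothesis test, for which the sample size is calculated, is that the true outcome is not greater than R_ul". The test is specified "with an α of .05 and a 1-tailed, 1-sample binomial test based on normal approximation (with continuity correction").

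For acceptability, the criterion is the proportion who "agree or strongly agree that the program is acceptable across all indicators >0.60", followed directly by the limits "R_ul_=0.55 and G_ll_=0.75". Table 3 repeats 55% and 75% and gives 80% power with N=40. It defines the denominator as the "percentage of those completing the program who agree or strongly that the program is acceptable across all domains". The first footnote to Table 2 likewise restricts the program acceptability indicators to participants who completed the module or program.

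The text introducing Table 3 says that a sample size of 100 gives more than 80% power for each focal outcome.

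**The concern.** Because the null is that the true proportion does not exceed the red limit, the value written after the greater-than sign should be that limit. It is for teenager initiation (0.50 and 0.50) and, within the text, for program completion (0.30 and 0.30). For acceptability it is not: 0.60 against 0.55. Nothing in the article makes 0.60 an amber cut-off or a separate rule for the observed rate.

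The criterion feeds the decision on progression to a main trial, and acceptability is the study's first objective. If each value were used as the null with 40 completers, the exact test would reject at 28 of 40 (70%) against 0.55 but would need 30 of 40 (75%) against 0.60. A result of 28 or 29 would pass under one and fail under the other.

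Separately, the sample of 100 is dyads enrolled, while the acceptability test uses only those who complete and answer. The power sentence does not say so.

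**Working it through.** **Inputs.** One-sided alpha 0.05 (z = 1.645), target power 80% (z = 0.842), and a one-sample binomial test by normal approximation with continuity correction, all from the Power section. Green limit p1 = 0.75. Red limit p0 = 0.55 (labelled limit and Table 3) or 0.60 (the value after the greater-than sign). One response per dyad is an assumption: mothers and teenagers are both surveyed, and the article does not say how their answers enter this test.

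**Formulas.** With d = p1 − p0:

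- n0 = [(1.645·√(p0(1−p0)) + 0.842·√(p1(1−p1))) / d]²
- corrected n = (n0/4)·[1 + √(1 + 2/(n0·d))]²
- power = Φ{[d − 1/(2n) − 1.645·√(p0(1−p0)/n)] / √(p1(1−p1)/n)}

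**Reproducing Table 3.**

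| Row | p0, p1 | Corrected n | Table 3 |
|---|---|---|---|
| Enrollment | 0.60, 0.75 | 67.4 | 68 |
| Acceptability | 0.55, 0.75 | 39.8 | 40 |
| Initiation | 0.50, 0.65 | 73.08 | 73 |
| Completion, per group | 0.25, 0.50 | 24.4 | 25 |

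The formula recovers every row (73.08 is printed as 73). For acceptability, n0 = [(0.818 + 0.364)/0.20]² = 34.97, which the correction raises to 39.8. At n = 40 the power is Φ[(0.20 − 0.0125 − 0.1294)/0.0685] = Φ(0.849) = 80.2% (exact binomial 82.1%). N=40 is correct for 0.55.

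**If 0.60 were the null.** n0 = [(0.806 + 0.364)/0.15]² = 60.9, corrected to 67.4, so 68. Table 3's enrollment row, with the same 60% and 75% limits, prints 68. At n = 40 the power is Φ[(0.15 − 0.0125 − 0.1274)/0.0685] = Φ(0.147) = 55.9% (exact 58.4%).

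**Power by number of completers with survey data** (continuity-corrected normal approximation):

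| Completers | Red limit 0.55 | Red limit 0.60 |
|---|---|---|
| 30 | 66.6% | 43.1% |
| 40 | 80.2% | 55.9% |
| 50 | 88.7% | 66.5% |
| 68 | 96.2% | 80.4% |

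**How many completers 100 dyads supply.** The binomial probability of at least 40 completers among 100 is 0.98 if the true completion rate is 50% (the plan's green limit), 0.54 at 40%, and 0.02 at 30% (the red limit in the text). With exactly 50 completers, 40 usable responses need a survey return of 40/50 = 80%. The 68 completers needed under 0.60 exceed both the 50% green limit and the booklet trial's figure in the Background section, where "62% of families reported completing the final booklet".

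**The case against.** The strongest reply is that the tested limit is already fixed. The number labelled as the red limit is 0.55, Table 3 repeats it, and the null is defined by that label; a lone unlabelled 0.60 does not displace them. That stands, and it rules out a stronger reading that a reader might infer: that Table 3 is miscalculated, or that the study has only 56% power for acceptability. The 56% requires 0.60 to be the null value, which the plan's own labels contradict.

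Nor would 0.60, read as a bar for the observed rate, overturn a pass. The exact test against 0.55 rejects at 28/40 (70%), 34/50 (68%) and 64/100 (64%), and for every n from 10 to 100 the rejection bar stays above 63%. The uncertainty then left concerns observed rates between 0.60 and the rejection bar.

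The pattern argument from the other items is modest. The enrollment item has no greater-than value, and the 0.30 in the completion item is itself at odds with the 25% in Table 3, which is a separate matter.

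On the denominator, Table 3 does say completers, and at the plan's green completion limit 100 dyads supply enough of them. At 30% completion the study would sit at its red limit for completion in any case. No survey return rate is given, so the 80% return is a break-even figure and not a predicted shortfall. What remains is that the power sentence is unconditional although the quantity is not.

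**Conclusion.** The point holds as an internal inconsistency in a decision threshold, of moderate severity. It is not an arithmetic error in Table 3. Three of the plan's own elements agree on 0.55 (the labelled limit, the null definition and N=40), so 0.60 is most likely a leftover, though the article does not settle this.

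The power statement for acceptability holds only with about 40 or more completers who return the survey. That is likely if completion reaches 50%, close to even at 40%, and very unlikely at 30%; these chances count completers and make no allowance for survey non-return. All figures assume one response per dyad and the stated one-sided, continuity-corrected test.

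**What to change.** 1. In the acceptability item of the Power section, change the value after the greater-than sign from 0.60 to 0.55, so that one red limit governs. Table 3, N=40 and the enrolled sample stay as they are.
2. Add a sentence stating that power for acceptability is conditional on the number of completers with survey data: about 89% at 50, 80% at 40 and 67% at 30. State whether the unit is the dyad, the mother or the teenager.
3. Only if the sponsor intends 0.60 as the red limit: change the acceptability row of Table 3 to 60% and N=68, and restate the power (about 56% at 40 completers, 66.5% at 50).

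The first two steps cost one number and a sentence or two. The third would mean giving up the claim of more than 80% power for this outcome unless about 68 of the 100 dyads complete and respond.

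### The Power section prints bare inequalities beside a one-sided test of the red limit, does not say which decides progression, and the two disagree

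*Protocol article*

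**What the plan says.** All of this stands in the protocol article, Statistical Analysis, Power, and in Table 3.

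- **A test.** "Hypothesis testing for binary feasibility outcomes tests against being in the red zone (unacceptable outcome"). The null hypothesis used for sizing "is that the true outcome is not greater than R_ul", where R_ul is the upper limit of the red zone. Table 3 is calculated "with an α of .05 and a 1-tailed, 1-sample binomial test based on normal approximation (with continuity correction").
- **Limits and inequalities.** The limits are introduced as "The point estimates that will be considered the red zone upper limit" and its green counterpart. Three of the four outcomes also carry a bare inequality. Initiation reads "the proportion of those enrolled who initiated the use of the program with their teenager >0.50", with a red limit of 0.50 and a green limit of 0.65, and completion reads "the proportion of those enrolled who completed the program >0.30 (R_ul_=0.30 and G_ll_=0.50"). Acceptability has >0.60 beside a red limit of 0.55 and a green limit of 0.75. Enrollment (0.60 and 0.75) has no inequality.
- **Table 3.** The required N is 68 for enrollment, 40 for acceptability, 73 for initiation and 25 per group for completion. The completion row uses a red limit of 25%, where the text has 0.30.

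The Overview of the Statistical Analysis section plans descriptive summaries of the feasibility and acceptability indicators and does not mention the one-sample tests.

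**The concern.** The article says that criteria fixed in advance will govern progression to the main trial. A reader who holds the results must know what observed result clears an outcome of the red zone. The only such figures printed on the scale of an observed proportion are the inequalities and the zone limits. The test, from which alpha and power come, needs a clearly higher observed rate, and no minimum count or rate is given for it.

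The two readings can lead to opposite conclusions from the same data. If 55 of 100 dyads start the program with the teenager, the >0.50 figure is met, yet the test does not reject the red limit. With the rule left open, the choice could be made after the data are seen. The Discussion expects this study to settle whether the program merits rigorous testing, so the choice matters.

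**Working it through.** **1. Which rule do the printed alpha and power belong to?** Inputs: one-sided alpha .05 (z = 1.645), power 80% (z = 0.8416), and Table 3's red limit p0 and green limit p1.

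Uncorrected: n0 = [(1.645·√(p0(1−p0)) + 0.8416·√(p1(1−p1))) / (p1−p0)]²

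Continuity-corrected: n = (n0/4)·[1 + √(1 + 2/(n0·(p1−p0)))]²

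Initiation (0.50 against 0.65): n0 = [(0.8224 + 0.4014)/0.15]² = 66.6, and the correction gives 73.1.

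| Outcome | Table 3 | One-sided, corrected | One-sided, uncorrected | Two-sided, corrected |
|---|---|---|---|---|
| Enrollment | 68 | 67.4 | 60.9 | 84.5 |
| Acceptability | 40 | 39.8 | 35.0 | 49.7 |
| Initiation | 73 | 73.1 | 66.6 | 91.4 |
| Completion, red 25% | 25 | 24.4 | 20.5 | 29.7 |

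Only the one-sided corrected test reproduces the table, so alpha and power describe that test. With the text's 0.30, completion would need 39.3, that is 40 per group.

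**2. Smallest count under each rule.** The inequality is met at the first count above n times the printed figure. The test rejects from c = ceil(n·R + 1.645·√(n·R(1−R)) + 0.5), where R is the red limit. For initiation at n=100, 50 + 8.22 + 0.5 = 58.72, so c = 59. For completion at R 0.30 and n=100, 30 + 7.54 + 0.5 = 38.04, so c = 39. The exact binomial test gives the same counts for every row below.

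**3. Chance of passing when the true rate equals R.** This is the exact binomial P(X ≥ count) at R. Power is the same probability at the green limit.

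| Outcome, n, red limit | Inequality met from | Passes at red limit | Test rejects from | Size of test | Power of test |
|---|---|---|---|---|---|
| Initiation, 100, 0.50 | 51 | 46.0% | 59 | 4.4% | 91.2% |
| Completion, 100, 0.30 | 31 | 45.1% | 39 | 3.4% | 99.0% |
| Completion, 25, 0.30 | 8 | 48.8% | 12 | 4.4% | 65.5% |
| Completion, 25, 0.25 | 8 | 27.3% | 11 | 3.0% | 78.8% |
| Completion, 100, 0.25 | 31 | 10.4% | 33 | 4.5% | above 99.9% |
| Acceptability, 40, 0.55 | 25 | 21.4% | 28 | 3.9% | 82.1% |
| Acceptability, 50, 0.55 | 31 | 19.7% | 34 | 4.3% | 90.2% |
| Enrollment, 120, 0.60 | none printed | not applicable | 82 | 3.7% | 96.1% |

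The rules disagree wherever the count lies between the two thresholds: 51-58 of 100 for initiation, 31-38 of 100 for completion at 0.30, and 25-27 of 40 for acceptability.

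**Source of n.** 100 is the planned enrollment, 25 the group size and 40 Table 3's N. The 120 eligible dyads come from the Recruitment section. The 50 completers are an assumption: 100 times the 0.50 green limit for completion.

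**The case against.** The strongest reply is that the article names its decision basis: hypothesis testing against the red zone, with the null stated. It nowhere says that an observed proportion above the printed figure satisfies a criterion. For initiation and completion the inequality equals the text's red limit, so it can be read as the alternative hypothesis about the true rate. Critical counts are also detail that an article may leave to the full protocol or analysis plan.

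Much of this stands. The inequalities cannot be called the plan's rule, and the absence of counts alone would be no finding. But the alternative-hypothesis reading fails for acceptability, where >0.60 stands beside a red limit of 0.55. The article itself prints the competing thresholds, so the conflict is not an omission left to another document.

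Two further replies also stand:

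- The percentages hold only at the red boundary. For initiation at n=100, a true rate of 0.45 exceeds 0.50 in 13.5% of studies, and 0.40 in 1.7%. Alpha, however, is defined at that same boundary, so the comparison with 5% is like for like.
- Leaving red is not reaching green. At a true rate equal to the red limit, the green limit is reached with probability 0.2% for initiation and below 0.01% for completion (0.30, n=100).

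**Conclusion.** The point holds as an ambiguity that changes conclusions. Two criteria are printed, only one has the stated error rates, and the article does not say which decides. If the inequalities are used as cut-offs, the pass rate at the red limit is 45-49% for initiation at n=100 and for completion at 0.30. It is 10-27% for completion at Table 3's 25%, and about 20-21% for acceptability at n=40-50. The test allows at most 5%.

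A reader might infer more, and the documents do not support it:

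- **That the plan accepts a 45-50% false-positive rate for progression on every outcome.** The test is named, enrollment has no inequality, the acceptability and 25% completion figures are lower, and clearing red is not the same as progressing.
- **That the 80% is offered as the chance of a green result.** Footnote a to Table 3 correctly labels it as power to reject red when green holds.

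The figures assume independent dyads and the sample sizes listed above. The actual numbers of completers and of eligible dyads will shift the counts for acceptability and enrollment.

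**What to change.** 1. State in the Power section that an outcome is cleared of red only if the one-sided .05 test rejects its red limit.
2. Delete the three inequalities, including the >0.60 that does not match 0.55.
3. Add a column of minimum counts to Table 3: 59/100 for initiation, 82/120 for enrollment if 120 dyads are eligible, and 28/40 for acceptability (34/50 if there are 50 completers). Say that the counts will be recalculated by the same formula for the denominators actually reached.
4. For completion, first reconcile the text's 0.30 with Table 3's 25%, and say whether the test is within group, as Table 3 sizes it, or over all enrolled dyads, as the text words it. At n=25 the minimum is 12 with 0.30 or 11 with 0.25. Keeping 0.30 within groups of 25 means accepting about 65% power.

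The cost is a few sentences and one table column, with no extra data. The downside is that observed rates just above the red limit no longer count as cleared.

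### The program-completion progression criterion is defined in two ways: red limit 0.30 among all enrolled in the text, red limit 25% within each group of 25 in Table 3

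*Protocol article*

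**What the plan says.** All the material is in the Power section of the protocol article (Methods, Statistical Analysis).

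- **Purpose.** The criteria are set in advance to judge progression to a main trial. The sizing rule is that "an adequate sample size is that which gives high power (≥80%) to reject being in the *red zone* if the *green zone* holds true". The null hypothesis is that the true proportion does not exceed the red upper limit.
- **Text.** Completion is given as "the proportion of those enrolled who completed the program >0.30", with a red upper limit of 0.30 and a green lower limit of 0.50. The denominator is everyone enrolled.
- **Table 3.** The row is labelled "Program completion rate (within group; percentage of those assigned to the group who complete all 6 program modules"), with a red limit of 25%, a green limit of 50%, power of 80% and a required sample of "25 (per group; 100 overall").
- **Link between them.** The article states: "Table 3 shows that a sample size of 100 provides >80% power to reject the null hypothesis across each" of the focal outcomes, "with an α of .05 and a 1-tailed, 1-sample binomial test based on normal approximation (with continuity correction").

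Elsewhere, the list of feasibility outcomes (program uptake and adherence) also counts completion among enrolled participants, and the abstract gives four groups of 25 dyads.

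**The concern.** The text and the table disagree on two features of one criterion: the red limit (0.30 or 0.25) and the denominator (all enrolled or each group). For the other three focal outcomes, the red and green limits in Table 3 match those in the text. Completion is the only row that departs.

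Two things are at stake. First, the same data could clear the red zone on one definition and stay in it on the other. A choice made after the data are seen would defeat the purpose of an a priori criterion. Second, completion is the only Table 3 row that leads to 100 dyads; the others need 68, 40 and 73. The stated reason for the total therefore depends on which completion test is meant.

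**Working it through.** **Inputs (Power section and Table 3).** One-sided α = .05, so z = 1.645; power 80%, so z = 0.842. The test is a one-sample binomial by normal approximation with continuity correction. Red limit p0 is 0.25 (Table 3) or 0.30 (text); green limit p1 is 0.50 in both; n is 25 per group or 100 overall.

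**Formulas.**
- Uncorrected size: n0 = [(1.645·√(p0(1−p0)) + 0.842·√(p1(1−p1))) / (p1−p0)]²
- Corrected size: n = (n0/4)·[1 + √(1 + 2/(n0·(p1−p0)))]²
- Power = Φ{[(p1−p0) − 1/(2n) − 1.645·√(p0(1−p0)/n)] / √(p1(1−p1)/n)}

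**Step 1: reproduce Table 3.**
- Completion, 0.25 vs 0.50: n0 = [(1.645×0.4330 + 0.842×0.5)/0.25]² = 20.5; corrected n = 24.4, so 25. This agrees with the table.
- The other rows give 67.4 (68 stated), 39.8 (40 stated) and 73.1 (73 stated), so this is the method that was used.

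The 25% in the completion row was therefore a real input to the calculation, not a misprint in the table or damage from text extraction.

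**Step 2: power of each stated version.**
- Table 3's version (0.25 vs 0.50, n = 25): (0.25 − 0.02 − 1.645×0.0866)/0.1 = 0.875; power 80.9%.
- The text's version (0.30 vs 0.50, n = 100): (0.20 − 0.005 − 1.645×0.0458)/0.05 = 2.39; power 99.2% (exact binomial 99.0%).

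**Step 3: required size at the text's red limit.** 0.30 vs 0.50: n0 = [(1.645×0.4583 + 0.842×0.5)/0.20]² = 34.5; corrected n = 39.3, so 40.

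**Step 4: the mixed case, 0.30 tested within a group of 25.** (0.20 − 0.02 − 1.645×0.0917)/0.1 = 0.29; power 61.5% (exact 65.5%). By step 3, 80% would need 40 per group.

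**Step 5: what the difference does to decisions.** The smallest count r that rejects satisfies (r − 0.5 − n·p0)/√(n·p0(1−p0)) ≥ 1.645.

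| n | Red limit 25% | Red limit 30% |
|---|---|---|
| 100 | 25 + 0.5 + 1.645×4.330 = 32.6, so 33 | 30 + 0.5 + 1.645×4.583 = 38.04, so 39 |
| 25 | 6.25 + 0.5 + 1.645×2.165 = 10.3, so 11 | 7.5 + 0.5 + 1.645×2.291 = 11.8, so 12 |

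With 100 enrolled, 33 to 38 completers clear a 25% limit but not a 30% one. The denominator matters too. As an illustration, 10 completers in every group make 40 of 100: this clears the text's overall test (39 or more), yet no group reaches Table 3's cut-off of 11.

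**The case against.** The strongest reply is that the power claim survives. Each definition, taken with its own limit and its own denominator, has more than 80% power, and Table 3's figure of 25 per group is correct for its inputs. That stands. A reader might infer that the study is underpowered for completion, at about 62%. The documents do not support this: the figure needs the text's limit joined to the table's denominator, and neither place states that test. It applies only if the authors say that this is what they meant.

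Three other stronger readings also fail.
- **An arithmetic error.** There is none; every Table 3 row reproduces to within rounding.
- **A limit lowered to make 25 per group work.** At 25 per group, 80% power does depend on the 25% limit, but the article does not show which figure came first or whether either is a slip.
- **A multiplicity failure across four group tests.** The article does not say whether all groups, or any one, must clear the red zone. An error rate for the combined decision would rest on a rule it does not contain, and such a rule may properly sit in a fuller document.

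It can also be said that this is a feasibility study and that the two limits differ by only one dyad within a group. That is true per group, but the gap is six dyads at n = 100 (33 against 39), and these criteria are the declared basis for both progression and sample size.

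**Conclusion.** The inconsistency is real and sits in the current text. The completion criterion has two red limits and two denominators, and no sentence says which governs. The sentence that presents Table 3 as showing more than 80% power for each focal outcome holds for the table's own completion test, but the table contains no calculation at the 0.30 limit that the text declares. A go/no-go threshold is therefore wrong as written and needs correcting before it is applied.

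The consequence is an undetermined decision, not a shown loss of power: results of 33 to 38 completers out of 100, or 11 out of 25, are classified differently by the two limits. These figures assume the declared one-sided .05 test with continuity correction, exactly 100 enrolled and exactly 25 per group. The article does not show which version is intended.

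**What to change.** State one red limit and one denominator for completion, identically in the text and in Table 3, and restate power and N to match. The choice is the authors'. Each option has its own consequence:

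1. **Overall test, 0.30 vs 0.50, all enrolled.** Change the Table 3 row. Power with 100 dyads is about 99% and about 40 are needed. The completion row then no longer justifies N = 100; the largest remaining requirement in Table 3 is 73, so the reason for 100 must be restated.
2. **Within-group test, 25% vs 50%.** Change the text to 0.25 and to those assigned to each group. Power is about 81% with 25 per group, and the table row stands.
3. **Within-group test, 0.30 vs 0.50.** Change the table's red limit and restate power as about 62% with 25 per group (40 per group would be needed for 80%). The claim of more than 80% power for every focal outcome must then be withdrawn for completion.

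Options 1 and 2 cost only wording in the Power section and, for option 1, one table row. Option 3 costs the same in wording if the lower power is accepted. None of the three adds participants unless the authors choose option 3 and also want 80% power.
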